#### Relevant concomitant care permitted or prohibited during the trial {11d}

Receiving other care during the intervention is not grounds for exclusion. The use of other, parallel care will be assessed after the intervention.

#### Provisions for post-trial care {30}

Participants with a continued need for care will be referred to different levels of care provided by the Stockholm Centre for Dependency Disorders, including digital interventions open to residents of all Swedish regions. Participants may also be encouraged to seek care within the municipality or the region to which they belong.

#### Outcomes {12}

Measurements will be made at registration (screening), before (week 0), during (week 4), and after the 8-week intervention (primary end-point, week 8), as well as at a 3-month follow-up (FU3), 6-month follow-up (FU6), and lastly at a 12-month follow-up (FU12). Measurements will take place in the form of self-assessment surveys via the secure digital treatment platform and supplemented with interview data from telephone interviews at week 0, week 8, and FU6. If there are sufficient resources available, a telephone interview may also be done at FU12.

### Primary outcome

The main outcome will be changes from baseline in standardized drinks (corresponding to 12 g of ethanol) per week, self-rated (number of drinks the previous week) at the post intervention time point. A decreased number of drinks per week is associated with improved quality of life and fewer alcohol-related consequences. Optimization criteria will be applied to the primary outcome regarding how effective the intervention is at reducing alcohol consumption at week 8 and how this is related with the clinician time spent on guidance (see the “Research questions” section).

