#### Sample size {14}

Statistical power was calculated using the R-package MOST for factorial optimization studies [29] to be able to detect a main between-group effect corresponding to Cohen’s *d* = 0.35. This calculation showed that 259 participants is sufficient. A small to moderate between-group effect size of 0.35 has been used in previous studies of support functions such as guidance in digital interventions [11, 30]. In a meta-analysis of digital interventions for problem drinking, guided interventions rendered 6.8 standard drink greater reductions than unguided interventions, which also speaks for a small to moderate effect of guidance [4]. With a margin for data loss, we aim to recruit a total of up to 300 participants. See Table 2 for target sample per group.

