### Assignment of interventions: allocation

#### Sequence generation {16a}

After inclusion, participants will be allocated randomly (1:1) to factor 1 (mid-treatment phone call) as well as (1:1) to factor 2 (weekly written guidance), resulting in four even arms (1:1:1:1). Randomization will be based on a true random number generator (http://www.random.org). There is no stratification of the randomization procedure.

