### Statistical methods

#### Statistical methods for primary and secondary outcomes {20a}

Main and interaction effects will be estimated based on all available measurement points using mixed models with the appropriate family function. Incremental cost-effectiveness ratios will be calculated where the main effect in spent clinician time of a factor is divided by the main effect in alcohol consumption. The uncertainty in data for incremental ratios will be handled using nonparametric bootstrapping. An optimization criterion with the best possible effect on alcohol consumption given a maximum of 1 h of clinician time per participant will also be explored in order to select an optimal combination of guidance.

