#### Methods in analysis to handle protocol non-adherence and any statistical methods to handle missing data {20c}

Analysis will be intention-to-treat, i.e., without consideration of non-adherence and with estimation of missing data. We intend to conduct random effects modeling or similar statistical analyses which uses all available data to estimate missing data, without the need for imputation.

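### The primary outcome is a change from baseline with no stated baseline adjustment; adjusting for week-0 drinks would give a more precise comparison at almost no cost

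*Protocol article*

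**What the plan says.** The Primary outcome section fixes the outcome: "The main outcome will be changes from baseline in standardized drinks" per week, self-rated for the previous week, at the post-intervention time point. Outcomes {12} lists week 0 among the repeated assessments: "Measurements will be made at registration (screening), before (week 0), during (week 4), and after the 8-week intervention (primary end-point, week 8"), with follow-ups to 12 months after that.

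The analysis is in section {20a}: "Main and interaction effects will be estimated based on all available measurement points using mixed models with the appropriate family function". Section {20c} adds: "We intend to conduct random effects modeling or similar statistical analyses which uses all available data to estimate missing data, without the need for imputation". None of these sections names baseline drinks as a covariate or places a constraint on the baseline means.

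Sample size {14} sets out "to be able to detect a main between-group effect corresponding to Cohen’s" d of 0.35 and concludes: "This calculation showed that 259 participants is sufficient". It does not say whether d is scaled on the SD of weekly drinks or on the SD of their change. The recruitment target is up to 300.

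**The concern.** The article defines the outcome as a change and points to a mixed model that uses every measurement. A natural implementation puts week 0 in as one of the repeated outcomes, with fixed effects for the factors, time and their products. That model looks as if it handles baseline, but with free baseline means in each arm it does not adjust for it. The effect on change is then the raw difference in change scores, which carries the full noise of the baseline measurement.

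Here baseline is one self-reported week of drinking, so the week-0 to week-8 correlation may be modest. The lower the correlation, the more precision is lost relative to adjustment. At stake are the main effects, the interaction (which is harder to estimate), and the cost ratios, whose denominators are the effects on alcohol consumption.

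**Working it through.** **Inputs.** d = 0.35 and N = 259 from Sample size {14}; two two-level factors with 1:1:1:1 allocation from Trial design {8}. Two-sided 5% and 80% power are assumed, because the article states neither. The correlation r between week-0 and week-8 drinks is not in the document, so a range is shown. SDs at the two times are first taken as equal.

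**1. The plan's own figure.** A main effect compares two halves of the sample. By the normal approximation, N = 4(1.960 + 0.842)²/0.35² = 256.3, which rounds up to 129 per factor level, or 258. The noncentral t calculation for an effect-coded main effect gives 259 (power 0.801). The 259 reproduces.

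**2. What the free-baseline model estimates.** With complete data, an identity link and a separate mean for every arm at every time, the fitted means are the observed cell means. The week-8 factor-by-time effect is therefore (week-8 mean minus week-0 mean at one factor level) minus the same quantity at the other level. That is the unadjusted change-score contrast.

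**3. Variances.** In units of the raw variance:

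- change score: 2(1 − r)
- baseline-adjusted: 1 − r²
- ratio, adjusted to change: (1 − r²)/[2(1 − r)] = (1 + r)/2

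With unequal SDs s0 and s8, the change-score variance exceeds the adjusted variance by (s0 − r·s8)², which is never negative. Apart from the negligible cost of estimating one slope, adjustment does not lose.

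**4. Power if d = 0.35 is on the raw SD.** Power = Φ(0.35·√259/(2√v) − 1.96), where v is the variance from step 3 and 0.35·√259/2 = 2.816.

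| r | v, change | v, adjusted | ratio | power at 259, change | power at 259, adjusted | N for 80%, change | N for 80%, adjusted |
|---|---|---|---|---|---|---|---|
| 0.3 | 1.40 | 0.91 | 0.65 | 66% | 84% | 360 | 234 |
| 0.5 | 1.00 | 0.75 | 0.75 | 80% | 90% | 258 | 194 |
| 0.7 | 0.60 | 0.51 | 0.85 | 95% | 98% | 154 | 132 |

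Worked line at r = 0.3: 2.816/√1.40 = 2.380, less 1.960 is 0.420, and Φ = 0.66; 2.816/√0.91 = 2.952, less 1.960 is 0.992, and Φ = 0.84.

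**5. If d = 0.35 is on the SD of change.** Then 259 gives the change score 80% power at any r. Adjustment still helps: 80% power would need 168, 194 or 218 participants at r = 0.3, 0.5 or 0.7.

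**The case against.** The strongest reply is that the article does not choose the less efficient model. It does not say that the analysis is unadjusted, that a subtracted score is the response, or that baseline means are free by arm. A condensed article commonly leaves covariates, family and link to the analysis plan, which is not shown. This stands in part: the loss is conditional on how the mixed model is set up. But the outcome itself is fixed as a change, and no adjustment is stated with it. Nor does including week 0 as a repeated measure remove the loss, as step 2 shows; only a covariate or a constraint on the baseline means does.

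A reader might be tempted to go further in four ways, none of which the document supports.

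- **That 259 is too few.** This would need d on the raw SD and r below about 0.5. Neither is stated, and at r = 0.7 the change score has 95% power.
- **That the model cannot be fitted because changes can be negative.** The article says only "using mixed models with the appropriate family function" and names no count family or log link. A count family would be applied to weekly drinks, with change carried by the time terms.
- **That the cost ratios are on the wrong scale.** No scale is fixed, and the outcome is in drinks per week. Even under a log link, standardised predictions return differences in drinks: a simulated negative binomial example gave −1.95 against a true −1.96.
- **That "There is no stratification of the randomization procedure" marks a fault.** Unstratified allocation is valid, and chance imbalance is already part of the standard error.

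**Conclusion.** The point holds as one of efficiency. The stated outcome, analysed by a mixed model with free baseline means, is an unadjusted change-score comparison. Baseline adjustment would cut its variance to 0.65, 0.75 or 0.85 of that value at r = 0.3, 0.5 or 0.7. This rests on equal SDs, complete data and an identity link, and on an r that the document does not give. The gain is large at low correlation and small at high correlation.

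The sample size is not shown to be wrong, and the free-baseline analysis would not be biased. If the unseen analysis plan already adjusts for week-0 drinks or constrains the baseline means, the loss does not arise, and only the wording of the outcome needs to be aligned.

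**What to change.** Define the primary analysis as week-8 drinks per week with week-0 drinks as a covariate. Alternatively, keep week 0 in a longitudinal model and constrain its mean to be equal across the four arms, which randomization justifies. Either version keeps the mixed model and the use of all available data.

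If a non-identity link is chosen, obtain standardised mean week-8 drinks for each arm. Derive the main effects, the interaction and the cost ratios as differences in those means, inside the planned bootstrap.

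State in the sample-size section which SD d = 0.35 refers to.

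The cost is a few sentences in the analysis plan. Week-0 drinks are already collected, and neither the design nor the recruitment target changes.

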### Secondary outcomes

Diagnostic criteria Alcohol Use Disorder [22]

Credibility/Expectancy Questionnaire [23]

Alcohol Use Disorders Identification Test [19]

Brunnsviken Brief Quality of Life Scale [24]

Penn Alcohol Craving Scale [25]

Patient Health Questionnaire 9 [26]

Generalized Anxiety Disorder 7 [27]

Readiness To Change Questionnaire—treatment version [28]

Self-rated questions about any adverse effects of the intervention

See Fig. 1 for time points for all outcomes.

**Fig. 1 Fig1:**
[figure not shown]
Schedule of enrollment, intervention, and assessments. ALVA, name of intervention; AUD, alcohol use disorder; CEQ, Credibility/Expectancy Questionnaire; AUDIT, Alcohol Use Disorders Identification Test; BBQ, Brunnsviken Brief Quality of Life Scale; PACS, Penn Alcohol Craving Scale; PHQ-9, Patient Health Questionnaire 9; GAD-7, Generalized Anxiety Disorder 7; RTCQ, Readiness To Change Questionnaire—treatment version

#### Participant timeline {13}

See Fig. 1 for a detailed time schedule of enrollment, intervention, and assessments. If there are sufficient resources available for a telephone interview at FU12, we will also perform a diagnostic interview of alcohol use disorder at the FU12 time point.

#### Sample size {14}

Statistical power was calculated using the R-package MOST for factorial optimization studies [29] to be able to detect a main between-group effect corresponding to Cohen’s *d* = 0.35. This calculation showed that 259 participants is sufficient. A small to moderate between-group effect size of 0.35 has been used in previous studies of support functions such as guidance in digital interventions [11, 30]. In a meta-analysis of digital interventions for problem drinking, guided interventions rendered 6.8 standard drink greater reductions than unguided interventions, which also speaks for a small to moderate effect of guidance [4]. With a margin for data loss, we aim to recruit a total of up to 300 participants. See Table 2 for target sample per group.

#### Recruitment {15}

As mentioned above under the “Study setting {9}” section, participants will be recruited nationally in Sweden via advertisements on the patient community and support website Alkoholhjalpen.se as well as on digital search services or social media. Advertisements achieved a satisfying rate of participant enrollment in the previous smaller study of the intervention [13].

### Assignment of interventions: allocation

#### Sequence generation {16a}

After inclusion, participants will be allocated randomly (1:1) to factor 1 (mid-treatment phone call) as well as (1:1) to factor 2 (weekly written guidance), resulting in four even arms (1:1:1:1). Randomization will be based on a true random number generator (http://www.random.org). There is no stratification of the randomization procedure.

#### Concealment mechanism {16b}

The allocation sequence will be generated with the true random number generator by a person not otherwise involved with the study.

#### Implementation {16c}

The study administrators (MK, CS, and other clinical psychologists or psychology students with basic training in psychotherapy) will enroll participants. The allocation sequence will then be generated by a person blinded to the participants and who is not otherwise involved with the study. The study administrators will then assign the participants to the intervention groups in the digital platform according to the allocation sequence.

### Assignment of interventions: blinding

#### Who will be blinded {17a}

There will be no blinding of participants, care providers, or assessors, but to minimize placebo/nocebo effects, the information to participants is that all participants will receive the active intervention with only some differences in added guidance. The assigned mode of added guidance will be explained to the participant after randomization by the study administration and within the intervention. The main outcomes are self-rated by the participants. The data analysist will be blinded.

#### Procedure for unblinding if needed {17b}

N/A. No unblinding will be needed because there will be no blinding.

### Data collection and management

#### Plans for assessment and collection of outcomes {18a}

Self-rated assessments will be made at registration (screening), before (week 0), during (week 4), after the 8-week intervention (week 8), at a 3-month follow-up (FU3), 6-month follow-up (FU6), and lastly at a 12-month follow-up (FU12). Telephone interviews will be made by the study administrators at week 0, week 8, and FU6. If there are sufficient resources available, a telephone interview may also be done at FU12.

#### Plans to promote participant retention and complete follow-up {18b}

If data is missing for the primary outcome of standardized drinks per week at week 8, FU6 and possibly at FU12, the number of standardized drinks the preceding week will be assessed in the telephone interview and used to replace the missing data point. Telephone-administered self-report data has been shown to be able to reduce the impact of missing data [31].

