#### Data management {19}

All self-rated data will be entered by the participant and stored at a secure server at Karolinska Institutet. Interview data will be entered by the study administrator interviewing the participant into the same technical platform as the self-rated data and stored on the secure server at Karolinska Institutet. This study will use the BASS platform from the eHealth Core Facility at Karolinska Institutet for data management. Double data entry is not possible on the BASS platform; rather, all data is time-stamped. Range check will be conducted. No other data quality processes will be used.

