#### Adverse event reporting and harms {22}

Any adverse effects of the intervention will be measured at weeks 4 and 8 (during and immediately after the intervention) using self-rated questions. Adverse events in behavioral interventions usually entail stress or anxiety related to initiating a behavior change. No regulatory bodies will be contacted.

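### The week-8 telephone fallback recovers drinks but not the adverse-effects answers, so survey non-response may understate harms

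*Protocol article*

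**What the plan says.** Under Secondary outcomes, the protocol article lists "Self-rated questions about any adverse effects of the intervention". The section on adverse event reporting {22} fixes instrument and timing: "Any adverse effects of the intervention will be measured at weeks 4 and 8 (during and immediately after the intervention) using self-rated questions". Data management {19} gives the mode: "All self-rated data will be entered by the participant and stored at a secure server at Karolinska Institutet".

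The retention section {18b} sets the telephone rule. Its trigger is "If data is missing for the primary outcome of standardized drinks per week at week 8, FU6 and possibly at FU12", and its content is that "the number of standardized drinks the preceding week will be assessed in the telephone interview and used to replace the missing data point". Nothing there mentions adverse effects.

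The call itself is not limited to any arm. Section {18a} states: "Telephone interviews will be made by the study administrators at week 0, week 8, and FU6". Section {11a} describes a telephone interview after the intervention, and the introduction's list of basic components says that this interview covers the client's experiences and any need for more help.

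For missing data, {20c} relies on a model that "uses all available data to estimate missing data, without the need for imputation".

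**The concern.** A participant who has stopped using the platform but answers the week-8 call gives a value for the primary outcome and none for week-8 harms, although the interviewer is on the line.

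This matters if non-response is related to harm. Section {22} expects adverse events to be mainly stress or anxiety from starting a behaviour change, and a person so affected could plausibly stop filling in surveys. The missing answer would then depend on a harm that nobody recorded. A model fitted to all available data does not correct for that.

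The loss could also differ by arm. Half the participants get weekly messages and half get a mid-treatment call, and {6b} says that an extra interview could boost engagement. What is at stake is the accuracy of a reported secondary outcome. The article plans no data monitoring committee ({21a}) and no independent audit ({23}), so these self-ratings are its stated harms record.

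**Working it through.** **1. The rules side by side**

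| | Drinks per week | Adverse effects |
|---|---|---|
| Survey at week 8 | yes | yes |
| Week-8 call takes place | yes | yes |
| Call fills a missing answer | yes ({18b}) | not stated |

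**2. The one related figure in the plan.** Sample size {14} gives 259 participants for d = 0.35. Assuming two-sided alpha 0.05 and 80% power (the article states neither), n per factor level = 2 × (1.960 + 0.842)² / 0.35² = 128.2, rounded up to 129. The total is 258, which agrees with 259. The target of up to 300 then leaves a margin of (300 − 259)/300 = 41/300 = 13.7%. This margin concerns the main analysis. It is not a stated non-response rate for harms and serves below only as an assumed value of m.

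**3. Understatement.** Let m be the proportion with no harms answer, p the harm rate in responders and kp the rate in non-responders. The true rate is (1 − m)p + mkp and the reported rate is p, so

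reported/true = 1 / ((1 − m) + km).

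The documents do not give k. At m = 0.137:

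- k = 0.5: 1/0.9315 = 1.07 (overstated)
- k = 1: 1/1 = 1.00 (no bias)
- k = 2: 1/1.137 = 0.88
- k = 4: 1/1.411 = 0.71

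**4. Difference between factor levels.** Assume a true rate of 10% at both levels and 150 participants per level (Table 2). All response rates are assumptions.

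- (a) Response 90% versus 75%, unrelated to harm: 10% is seen at both levels. There is no bias, only fewer events (13.5 and 11.2 of 15).
- (b) Harmed respond 60% and unharmed 86% at both levels: 0.060/(0.060 + 0.774) = 7.2% at both. Harm is understated with no false difference.
- (c) Harmed/unharmed respond 80%/90% with guidance and 50%/80% without: 0.08/0.89 = 9.0% versus 0.05/0.77 = 6.5%, a false difference of 2.5 points.
- (d) k = 3 at both levels, with 10% missing versus 25%: 10/1.2 = 8.3% versus 10/1.5 = 6.7%, a false difference of 1.7 points.

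A false difference needs two things together: non-response related to harm, and an unequal amount or pattern of loss. In (d), with 135 and 112 responders, the standard error is √(0.083 × 0.917/135 + 0.067 × 0.933/112) = 3.3 points, so the false difference is about half a standard error.

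**The case against.** The strongest reply is that harms are not invisible to the trial. Late assessments can prompt a reminder call ({11c}), and reminders are not limited by arm. Clinicians phone participants with suicidal ideation or severe withdrawal, and participants can alert the clinician ({11b}). Surveys are "supplemented with interview data from telephone interviews at week 0, week 8, and FU6" ({12}), and the interview guide is not shown, so harms questions in the call cannot be excluded. There are two harms surveys, so a person who misses week 8 may have answered at week 4. Limiting telephone recovery to the primary outcome is a common way to spare participants, and {21a} describes the risk of harm as low.

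Much of this stands, and it rules out calling the self-ratings the trial's only sight of harm. It does not close the gap. The reminder call is optional and only prompts. Nowhere does the article say that interview, clinician-call or alert information enters the adverse-effects outcome. A week-4 answer cannot cover harm that arises later.

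A reader might also infer three stronger things that the document does not support:

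- **That loss is probably unequal across arms.** No response rates are given, {6b} speaks of engagement and not of survey completion, and unequal response alone does not bias the rates (scenario a).
- **That biased harms would steer the choice of components.** Trial design {8}, Primary outcome and {20a} name alcohol consumption and clinician time as the criteria, not harms.
- **That a planned comparison of harms between arms is distorted.** The article states no such comparison.

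**Conclusion.** The point holds in a limited form. As written, a week-8 survey non-responder who takes the planned call contributes drinks but no week-8 adverse-effects answer. If harmed participants respond less often, the reported rate is too low. A different degree of understatement by arm is possible but not shown.

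The size rests wholly on assumed values. The figures in step 3 treat harms as a single measurement, so they do not credit week-4 answers. The direction also depends on k being above 1, which is plausible but not documented. This is a weakness in capturing a secondary outcome and does not touch the primary analysis. It is worth correcting because the remedy uses a call that is already planned.

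**What to change.** In {22} and {18b}, add that when the week-8 adverse-effects items are missing, the same items are asked in the existing week-8 telephone interview, in all four arms, covering the time since the participant's last answered harms survey. The mid-treatment call should not serve this purpose, since only half the participants receive it and its use would itself make ascertainment differ by arm. Record the mode of each answer. Report harms with the number answering per arm, once with and once without telephone answers.

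The cost is a few minutes of call time for non-responders. Log it separately from guidance time, because clinician time enters the optimization criteria. Interviewers are unblinded ({17a}) and telephone answers may differ in candour, hence the mode flag and the two presentations. Those who decline both survey and call stay missing.

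The change may need permission from the ethics authority ({25}). It cannot recover participants already past week 8, but the article, dated June 2023, expects recruitment to run to Q4 2024, so later participants would benefit.
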